**Methods/Design:**

The overall goal of this study is to better understand the factors leading to successful dispatch-assisted CPR instructions and to ultimately save the lives of more cardiac arrest patients. The study will utilize a before-after, prospective cohort design to specifically: 1) Determine the ability of 9-1-1 dispatchers to correctly diagnose cardiac arrest; 2) Quantify the frequency and impact of perceived agonal breathing on cardiac arrest diagnosis; 3) Measure the frequency with which dispatch-assisted CPR instructions can be successfully completed; and 4) Measure the impact of dispatch-assisted CPR instructions on bystander CPR and survival rates.

The study will be conducted in 19 urban communities in Ontario, Canada. All 9-1-1 calls occurring in the study communities reporting out-of-hospital cardiac arrest in victims 16 years of age or older for which resuscitation was attempted will be eligible. Information will be obtained from 9-1-1 call recordings, paramedic patient care reports, base hospital records, fire medical records and hospital medical records. Victim, caller and system characteristics will be measured in the study communities before the introduction of dispatch-assisted CPR instructions (before group), during the introduction (run-in phase), and following the introduction (after group).

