## Objectives

The overall goal of this study is to better understand the factors leading to successful dispatch-assisted CPR instructions. This is essential in order to intervene to improve the effectiveness of these instructions, to further improve bystander CPR rates, and to save more victims of cardiac arrest. Specific objectives are to:

1) Determine the ability of Dispatch Officers to correctly diagnose cardiac arrest over the telephone;

2) Quantify the frequency and impact of perceived agonal breathing on cardiac arrest diagnosis by Dispatch Officers;

3) Measure the frequency with which dispatch-assisted CPR instructions can be successfully completed in out-of-hospital cardiac arrest cases; and

4) Measure the impact of dispatch-assisted CPR instructions on bystander CPR rates and survival for out-of-hospital cardiac arrest.

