## Methods

### Study design and setting

This study will combine a before-after design with a prospective cohort design (Figure 1). Objective 4 (bystander CPR and survival rates) will be addressed using a before-after design, the "before" phase occurring prior to 2004, and the prospective "after" phase starting in 2007 (after the run-in period). Objectives 1, 2, and 3 will be addressed with a prospective cohort starting in 2007. The prospective cohort group and the "after" group will be the same group.

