### Study population

All patients with out-of-hospital cardiac arrest (absence of a detectable pulse, unresponsiveness and apnea) meeting the following criteria will be enrolled in the study:

a) presumed cardiac origin;

b) occurring in an eligible study community; and

c) for which resuscitation is attempted by a bystander and/or the emergency responders; or for which dispatch-assisted CPR instructions are being provided.

Case definitions will follow the Utstein Style guidelines for reporting cardiac arrest data [1].

Patients meeting any of the following criteria will be excluded:

a) patients younger than 16 years (cardiac arrest usually respiratory and rare in this population);

b) patients who are "obviously dead" as defined by the Ambulance Act of Ontario (decomposition, rigor mortis, decapitation, or other);

c) trauma victims, including hanging and burns; or

d) patients with cardiac arrests clearly of other non-cardiac origin including drug overdose, carbon monoxide poisoning, drowning, exsanguination, electrocution, asphyxia, hypoxia related to respiratory disease, cerebrovascular accident, and documented terminal illness.

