### Method of assessment and data collection

#### Diagnosis of Cardiac Arrest by Dispatch Officers

According to protocols, Dispatch Officers assume the presence of cardiac arrest when the 9-1-1 caller describes a victim that is lifeless (victim is unresponsive, not breathing, or not breathing normally). Dispatch Officers will notify the medical dispatch centre after every occasion where assisted CPR instructions were initiated. Using a unique identifier, these interventions/cases will later be cross-referenced with the regional cardiac arrest registry for measuring diagnostic accuracy. In addition, a research assistant will later listen to the recordings of each cardiac arrest intervention and document on a standardized and piloted data collection form the reasons why cardiac arrest may not have been recognized by the Dispatch Officer.

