### Data analysis

#### Cardiac Arrest Recognition

Sensitivity, specificity and receiver operating characteristic (ROC) curves will be computed.

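### Inclusion criterion (c) admits an arrest without a resuscitation attempt if the dispatcher gave instructions but not if the dispatcher missed it, so Objective 1 sensitivity may be biased upward

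*Protocol article*

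**What the plan says.** The protocol article states eligibility twice, and the statements differ.

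- Abstract, Methods/Design: calls are eligible if they report an arrest in "victims 16 years of age or older for which resuscitation was attempted will be eligible". Instructions from the dispatcher give no route of entry.
- Methods, Study population, criterion (c): an arrest qualifies if it is one "for which resuscitation is attempted by a bystander and/or the emergency responders; or for which dispatch-assisted CPR instructions are being provided". Instructions alone are enough.

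The exclusions in the same Methods section apply to both routes. They remove, among others, "patients who are 'obviously dead' as defined by the Ambulance Act of Ontario" and patients with documented terminal illness.

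The cohort so defined serves Objectives 1 to 3. Study design and setting says: "The prospective cohort group and the 'after' group will be the same group". Objective 1 is to "Determine the ability of Dispatch Officers to correctly diagnose cardiac arrest over the telephone", and the analysis under Cardiac Arrest Recognition is one sentence: "Sensitivity, specificity and receiver operating characteristic (ROC) curves will be computed". On ascertainment, dispatchers report each occasion on which they started instructions, and "these interventions/cases will later be cross-referenced with the regional cardiac arrest registry for measuring diagnostic accuracy". The article does not give the registry's own inclusion rule.

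**The concern.** Sensitivity is the share of true arrests that the dispatcher recognised. Its denominator should not depend on what the dispatcher did.

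Take two identical arrests, neither meeting an exclusion, with no resuscitation attempt by responders or bystander. In the first, the dispatcher recognises the arrest and gives instructions that are not carried out. Criterion (c) enrols it, and it counts as a true positive. In the second, the dispatcher misses the arrest. It meets no part of criterion (c), so this false negative never enters. Among arrests that nobody tried to resuscitate, the rule keeps successes and drops failures.

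The Discussion says that Objective 1 will be used to find modifiable factors that could raise diagnostic accuracy. Missed arrests are the informative cases for that purpose, and the rule leaves some of them out. A larger sample does not reduce the bias.

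**Working it through.** **The plan's own figure.** The Sample size section gives 2,962 per group for survival of 5% versus 7% at 90% power. With a two-sided 5% level (assumed, as the section states none) and no continuity correction:

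n = [1.960·√(2·0.06·0.94) + 1.2816·√(0.05·0.95 + 0.07·0.93)]² / 0.02² = 1.1844 / 0.0004 = 2,961.02, rounded up to 2,962.

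The figure reproduces. It does not depend on this point and is used below only as the size of the after cohort.

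**Inputs from the pilot section**

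- Recognition: 56.0%.
- Instructions offered: 75.9%. The base is not stated; recognised cases are assumed.
- Bystander CPR before instructions were introduced: 16.7%. This is assumed to be the rate of spontaneous CPR in uninstructed arrests.

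**Assumptions not in the article**

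- u is the number of arrests not treated by responders, and not otherwise excluded, per treated arrest. It is varied over 0.1, 0.2 and 0.3.
- Recognition and instruction rates are the same in treated and untreated arrests.

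**Who enters, per untreated arrest**

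- Recognised and instructed, all enter: 0.56 × 0.759 = 0.4250.
- Recognised, not instructed, enter only with spontaneous CPR: 0.56 × 0.241 × 0.167 = 0.0225.
- Missed, enter only with spontaneous CPR: 0.44 × 0.167 = 0.0735.

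Recognised entrants total 0.4476 and all entrants 0.5211. Apparent sensitivity is therefore

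Se(u) = (0.56 + 0.4476u) / (1 + 0.5211u).

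| u | Numerator | Denominator | Apparent sensitivity | Bias (points) |
|---|---|---|---|---|
| 0 | 0.5600 | 1.0000 | 56.0% | 0 |
| 0.1 | 0.6048 | 1.0521 | 57.5% | +1.5 |
| 0.2 | 0.6495 | 1.1042 | 58.8% | +2.8 |
| 0.3 | 0.6943 | 1.1563 | 60.0% | +4.0 |

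**Against random error.** The 95% half-width at 2,962 arrests is 1.96·√(0.56·0.44/2962) = 0.0179, or 1.8 points. The bias reaches this at about u = 0.12: 0.12 × (0.4476 − 0.56 × 0.5211) / (1 + 0.5211 × 0.12) = 0.0176.

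**Second parametrisation.** Let v be the share with no attempt by anyone, among arrests without completed instructions. Every instructed arrest is enrolled, and uninstructed arrests are enrolled with probability 1 − v:

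Se(v) = (0.4250 + 0.1350(1 − v)) / (0.4250 + 0.5750(1 − v)).

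This gives 57.0%, 58.0%, 60.2% and 62.8% at v = 5%, 10%, 20% and 30%. Under an attempted-only rule like the Abstract's, the same model (with 8.3% of instructed arrests completed) gives 56.1% at 5% and 56.7% at 30%. Nearly all of the bias therefore comes from the instructions route.

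**The case against.** **The size cannot be shown from the article.** This stands. No section gives u, and the exclusions for obvious death and terminal illness remove many arrests that responders would leave untreated, whatever the dispatcher did. What remains could be small, and at u = 0 there is no bias. Equal recognition in treated and untreated arrests is also unsupported.

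**Not every arrest that enters without responder treatment is a success.** This stands and is built into the working. If all such entrants are counted as instructed, the added cases per treated arrest are 0.4250u and the bias comes out at +1.8, +3.4 and +5.0 points. Those figures are too high, because missed arrests with spontaneous bystander CPR also enter. Nor does every arrest with instructions enter, since the exclusions still apply. A recognised arrest with neither instructions nor an attempt is left out as well. That reduces the bias but does not reverse it.

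**The exact denominator may be set in the full protocol or SAP.** This stands only in part. The registry's rule is not given, and further detail may exist elsewhere. But the enrolment rule and the use of that cohort for Objective 1 are fixed in the article, and its two eligibility statements disagree.

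**A responder-treated denominator has its own selection.** Responders may be more willing to treat where a bystander is already giving CPR, so some dependence on the dispatcher remains. This is a weaker problem than entry on the dispatcher's own action and does not defend it.

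**Stronger readings that the article does not support.** A reader might infer that completion of instructions (Objective 3) is inflated too. Completion is defined as chest compressions by a bystander, so every completed case is already a bystander attempt. The instructions route can add only non-completions. Taking the pilot's 8.3% as a share of instructed cases (its base is not stated), completion per instructed case is 8.3% both in all arrests and as enrolled. Per arrest, at v = 20%, it is 3.5% in all arrests, 4.0% as enrolled and 4.4% under an attempted-only rule. The direction depends on denominator and comparator, and the article fixes neither. A reader might also infer distorted comparisons between communities, but community-level analysis is planned only for bystander CPR and survival.

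**Conclusion.** The point holds for Objective 1 as a potential upward bias of unknown size. Its direction follows from criterion (c): whenever some eligible arrests receive no attempt from anyone, enrolment favours those in which the dispatcher gave instructions.

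The illustrative range of +1.5 to +4.0 points for u between 0.1 and 0.3 rests on pilot rates, on assumed bases for two of them, and on a ratio that the article does not supply. It shows that the bias can match or exceed sampling error at modest u, not that it will. The conflict between the Abstract and the Methods needs no assumption. Objective 3 completion and the survival sample size are not called into question.

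**What to change.** 1. State that Objective 1 sensitivity is computed among arrests in which emergency responders attempted resuscitation, whatever the dispatcher did.
2. Report arrests that enter only through instructions or bystander CPR on a separate line, outside the sensitivity estimate.
3. Reconcile the eligibility statement in the Abstract with criterion (c) in Study population.

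This takes a sentence or two and no new data. In the illustration, the cases moved to the separate line are 0.5211u / (1 + 0.5211u) of those enrolled: 5.0%, 9.4% and 13.5% at u = 0.1, 0.2 and 0.3. At the largest of these, 2,962 enrolled arrests leave about 2,562 in the denominator, and the half-width rises from 1.8 to 1.9 points. The reported sensitivity will be slightly less favourable. Some selection remains if responders' decisions depend on ongoing bystander CPR, and this should be acknowledged when the result is reported.

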### Method of assessment and data collection

#### Diagnosis of Cardiac Arrest by Dispatch Officers

According to protocols, Dispatch Officers assume the presence of cardiac arrest when the 9-1-1 caller describes a victim that is lifeless (victim is unresponsive, not breathing, or not breathing normally). Dispatch Officers will notify the medical dispatch centre after every occasion where assisted CPR instructions were initiated. Using a unique identifier, these interventions/cases will later be cross-referenced with the regional cardiac arrest registry for measuring diagnostic accuracy. In addition, a research assistant will later listen to the recordings of each cardiac arrest intervention and document on a standardized and piloted data collection form the reasons why cardiac arrest may not have been recognized by the Dispatch Officer.

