### Ability of 9-1-1 callers to follow dispatch-assisted CPR instructions

Two studies of recorded 9-1-1 calls determined that CPR instructions were appropriate and possible in only 30% to 37% of all confirmed cardiac arrest cases [78,79]. While a majority of callers were emotionally capable of following instructions [75,80,81], the telephone was not in close range of the victim as often as 50% of the time [80-82]. Many of these studies are now more than 10 years old; with the introduction of cell phones and cordless phones, the ability of providing CPR instructions over the telephone likely has improved significantly.

It also appears that ventilation instructions over the telephone can be relatively time consuming. In a randomized, controlled study by Hallstrom, it took an additional 1.4 minutes to complete the mouth-to-mouth instructions compared to doing immediate chest compressions without ventilations [83]. In some cases, this additional delay can result in the paramedics arriving before the chest compressions are initiated. Although results from the Hallstrom study did not reach statistical significance, survival to hospital discharge appeared to favour the chest-compression only group compared to traditional CPR with ventilation instructions (14.6% vs. 10.4%; P = 0.18) [84]. Currently, most 9-1-1 dispatch centers no longer offer ventilation instructions to callers reporting a witnessed cardiac arrest victim whose collapse occurred less than 10 minutes prior to the call.

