#### Agonal breathing

Can be defined as abnormal breathing, gurgling sound, moaning, or otherwise. Dispatchers Officers are required by protocol to inquire about the presence or absence of agonal or abnormal breathing. A research assistant at each base hospital will systematically review the recordings of all cardiac arrest calls, and use a piloted data collection form to independently document the presence or absence of agonal breathing, as described by the 9-1-1 caller to the Dispatch Officer. Consistency in recognizing agonal breathing among research assistants will be assured with the use of training 9-1-1 communication material before the study starts.

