#### Dispatch-Assisted CPR Instructions

Descriptive statistics with 95% CIs will be calculated to describe successes in various stages of the implementation of CPR instructions, to describe the caller's receptiveness of the instructions, and various time delays occurring during dispatch-assisted CPR instructions.

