## Discussion

Dispatch-assisted CPR instructions are relatively new in the field of cardiac arrest resuscitation. Their delivery methods are based on limited scientific evidence, and need to be further optimized. This study will provide essential information on modifiable factors to improve the quality of dispatch-assisted CPR instructions, further improve bystander CPR rates, and save more cardiac arrest victims. First, we will identify modifiable factors that could increase the current cardiac arrest diagnostic accuracy of Dispatch Officers. Second, we will quantify the impact of agonal breathing on the Dispatch Officer's diagnostic accuracy in order to develop educational strategies designed to help them recognize this condition. Third, we will identify modifiable factors influencing the ability of 9-1-1 callers to comply with CPR instructions provided over the telephone. Finally, we will convincingly determine the impact of dispatch-assisted CPR instructions on bystander CPR and survival rates.

This information is essential to develop clinical trials testing a variety of educational approaches and delivery methods for telephone CPR instructions. This will be the first study worldwide to clearly quantify the impact of dispatch-assisted CPR instructions on survival to hospital discharge for out-of-hospital cardiac arrest victims. We anticipate our study will show that dispatch-assisted CPR instructions contributed to saving as many as 40 lives per year in the participating centres alone, and as much as 360 lives annually in Canada.

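### The goal of identifying factors behind recognition and completed instructions has no matching analysis: both outcomes are only described, and the only regression models are for bystander CPR and survival

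*Protocol article*

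**What the plan says.** All places are in the protocol article.

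- **Objectives.** "The overall goal of this study is to better understand the factors leading to successful dispatch-assisted CPR instructions". Objective 3 is narrower and asks for a frequency: "Measure the frequency with which dispatch-assisted CPR instructions can be successfully completed in out-of-hospital cardiac arrest cases".
- **Discussion.** Modifiable factors are promised for the dispatchers' diagnostic accuracy. For callers, "we will identify modifiable factors influencing the ability of 9-1-1 callers to comply with CPR instructions provided over the telephone". This information is presented as essential for developing later trials.
- **Data collection, recognition.** After listening to the recordings, an assistant will "document on a standardized and piloted data collection form the reasons why cardiac arrest may not have been recognized by the Dispatch Officer".
- **Data collection, agonal breathing.** On all cardiac arrest calls, assistants "independently document the presence or absence of agonal breathing, as described by the 9-1-1 caller to the Dispatch Officer".
- **Data collection, completion.** All cardiac arrest calls are reviewed on a piloted form for variables on successful delivery. The article does not list the items. Success requires bystander chest compressions before EMS arrives.
- **Data analysis, recognition.** Sensitivity, specificity and ROC curves.
- **Data analysis, agonal breathing.** Descriptive statistics and kappa.
- **Data analysis, instructions.** "Descriptive statistics with 95% CIs will be calculated to describe successes in various stages of the implementation of CPR instructions", and likewise for callers' receptiveness and for time delays.
- **Data analysis, bystander CPR and survival.** Logistic regression and a time series. The covariates listed for the regression are age, gender, initial rhythm and EMS response intervals.

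**The concern.** To say that a factor leads to success, one must compare how often it occurs in successes and in failures, or equivalently the success rate with and without it. A frequency with a confidence interval does not do this. Nor does sensitivity, or a kappa between dispatcher and assistant.

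The field for reasons why an arrest was missed has the same weakness at the point of collection. A reason for non-recognition exists only where recognition failed. A feature often cited in missed calls may be just as common in recognised ones, and this field cannot show it.

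The definition of success adds a further problem. A call in which the crew arrives before compressions begin is a failure, together with a call in which the caller could not or would not comply. The background acknowledges the first route, noting for ventilation instructions that "this additional delay can result in the paramedics arriving before the chest compressions are initiated". The two kinds of failure point to different remedies.

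At stake are the declared overall goal and the basis for the trials that are to follow.

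**Working it through.** **1. Promise against stated analysis**

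| Outcome | Promise (Objectives, Discussion) | Stated analysis | Factor related to outcome? |
|---|---|---|---|
| Recognition | Modifiable factors for diagnostic accuracy | Sensitivity, specificity, ROC | None stated |
| Agonal breathing | Its impact on diagnosis (objective 2) | Descriptive statistics, kappa | Intended by the objective; recorded on all calls |
| Completion | Modifiable factors for caller compliance | Descriptive statistics with 95% CIs | None stated |
| Bystander CPR, survival | Before-after effect | Logistic regression, time series | Age, gender, rhythm, EMS intervals; no caller, call or dispatcher factor listed |

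**2. Why a comparator matters: the pilot's own figures**

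In the pilot, 56.0% of arrests were recognised, so 44.0% were missed. Agonal breathing was present in 37.0% of all arrests and accounted for 50.0% of missed diagnoses. Assume that the latter means it was present in 50.0% of missed calls. Then its frequency in recognised calls is

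(37.0 − 0.44 × 50.0) / 0.56 = 15.0 / 0.56 ≈ 27%.

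The 50% is informative only beside the 27%. Recording agonal breathing on every call secures this contrast. The missed-arrest reasons field does not secure it for any other feature.

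**3. Is a factor analysis feasible?**

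The plan's own sample size comes first. Survival of 5% against 7% with 90% power gives 2,962 per group, which reproduces exactly with a two-sided 0.05 level (assumed; none is stated), pooled variance and no continuity correction. The point does not depend on that figure, but it sets the number of calls. Pilot rates are assumed to carry over.

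- Recordings located: 2,962 × 0.821 ≈ 2,432.
- Missed arrests: 2,432 × 0.44 ≈ 1,070.
- Callers offered instructions, if the pilot's 75.9% is of recognised arrests: 2,432 × 0.56 × 0.759 ≈ 1,034.
- Completions, if the pilot's 8.3% (chest compressions) is of all recorded callers: 2,432 × 0.083 ≈ 202.
- Completions, if the 8.3% is of callers offered instructions: 1,034 × 0.083 ≈ 86.

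At ten events per factor, 86 to 202 completions support roughly 8 to 20 factors. Recognition, with about 1,070 misses, is not limited in this way.

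Power was checked for one binary factor present in 30% to 50% of calls, using a two-proportion test at two-sided 0.05. The success rates p0 and p1, without and with the factor, are set so that the overall rate is as assumed and the odds ratio is as shown.

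| Calls compared | Completions | Power, OR 1.5 | Power, OR 2.0 |
|---|---|---|---|
| All recordings, 2,432 | 202 (8.3%) | 75–78% | 99% or more |
| Offered instructions, 1,034 | 202 (202/1,034 = 19.5%) | 69–73% | about 99% |
| Offered instructions, 1,034 | 86 (8.3%) | 42–43% | 84–85% |

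For example, in the last row at 50% prevalence and OR 1.5, p0 = 6.8% and p1 = 9.8%.

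For completion, strong factors could be found and modest ones might not be.

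**The case against.** The strongest case on the other side has four parts.

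- **Collection is broad.** A reader might infer from the missed-arrest field that information is gathered only on failed calls. The article does not support that. Delivery variables and agonal breathing are recorded on all cardiac arrest calls, and the abstract says that victim, caller and system characteristics will be measured. Whether features such as caller distance or emotional state are coded in recognised calls cannot be told, because the form's items are not listed. This part stands. Only the reasons field is one-sided.
- **Some comparison is intended.** A reader might also infer that no factor is ever compared between outcomes. That too goes beyond the text. Objective 2 relates agonal breathing to diagnosis, and descriptive statistics could be tabulated by outcome. This part stands as a limit on the claim.
- **The detail may be elsewhere.** The full protocol, any SAP and the figure on proposed analyses are not shown and may contain a model. This is a fair caution, but the point does not rest on silence. The article assigns an analysis to each topic and names models and covariates for bystander CPR and survival. What it assigns to recognition and completion does not support what the Discussion promises.
- **Objectives 1 and 3 ask only for ability and frequency.** The analyses match those two objectives. They do not match the overall goal above them or the Discussion.

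On crew arrival, success is to be described by stage and delays are to be reported, so the two kinds of failure may be partly visible. No stated analysis separates them. It is tempting to subtract the pilot's delays from its mean response interval to obtain a time margin before a crew overtakes a call. The article does not allow this. The two delays are not said to be means or consecutive, and the interval ends when the vehicle stops, not when the crew reaches the patient.

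**Conclusion.** The point holds as a mismatch between goal and analysis. As stated, the study will estimate how often arrests are recognised and instructions completed, and can contrast agonal breathing between recognised and missed calls. No stated analysis relates any other factor to recognition or completion, although finding such factors is the overall goal and the stated basis for later trials. One collection item, the reasons for missed arrests, lacks a comparator.

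The conclusion rests on the article's text alone. A factor model in an unseen document would answer the analysis part, but the article's wording would still need to agree with it. The event counts assume 2,962 after-phase cases and pilot rates. The range of 86 to 202 completions reflects an unclear denominator. These counts show feasibility; they do not measure the defect. The change should be made. It does not affect the before-after comparison of survival.

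**What to change.** 1. Under *Diagnosis of Cardiac Arrest by Dispatch Officers*, replace the free list of reasons for a miss with a presence/absence checklist scored on every recording, recognised or not.
2. Under *Cardiac Arrest Recognition*, add one prespecified logistic model for recognition among all arrests. Under *Dispatch-Assisted CPR Instructions*, add one for completed compressions among callers offered instructions. Each should have a short fixed list of caller and call factors, for example relation to the victim, distance from the victim, emotional state, prior CPR training, witnessed collapse and location. Report odds ratios with 95% CIs. Keep the completion list to about eight factors unless completions prove closer to 202 than to 86.
3. Report crew arrival before compressions as its own category of non-completion.
4. If the models are not wanted, narrow the overall goal and the Discussion to description.

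The cost is revised form wording, slightly more coding per recognised call and two extra models. Assistants already review the recordings of all cardiac arrest calls, so no new data source is needed.
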